# PARIS: protocol for a prospective single arm, theory-based, group-based feasibility intervention study to increase Physical Activity and reduce sedentary behaviouR after barIatric Surgery

**DOI:** 10.1136/bmjopen-2021-051638

**Published:** 2021-12-22

**Keywords:** rehabilitation medicine, diabetes & endocrinology, public health

## Abstract

**Introduction:**

Increased physical activity and reduced sedentary behaviour can encourage favourable outcomes after bariatric surgery. However, there is a lack of evidence as to how to support patients with behaviour change. The aim of this study is to assess the feasibility of a physiotherapist led, online group-based behaviour change intervention to increase physical activity and reduce sedentary behaviour following bariatric surgery.

**Methods and analysis:**

Single arm feasibility study of a theory and evidence-based group behaviour change intervention based on the Behaviour Change Wheel and Theoretical Domains Framework using behaviour change techniques from the Behaviour Change Technique Taxonomy v1. The intervention has eight objectives and specifies behaviour change techniques that will be used to address each of these. Groups of up to eight participants who have had surgery within the previous 5 years will meet weekly over 6 weeks for up to 1½ hours. Groups will be held online led by a physiotherapist and supported by an intervention handbook. Feasibility study outcomes include: rate of recruitment, retention, intervention fidelity, participant engagement and acceptability. Secondary outcomes include: physical activity, sedentary behaviour, body composition, self-reported health status and will be analysed descriptively. Change in these outcomes will be used to calculate the sample size for a future evaluation study. Qualitative interviews will explore participants’ views of the intervention including its acceptability. Data will be analysed according to the constant comparative approach of grounded theory.

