Evidence from systematic reviews and meta-analyses shows that patients who are more physically active after bariatric surgery optimise their weight and fat mass loss and improved their fitness compared with those who do not.^10 11^ Evidence from a randomised control trial of 60 patients with a BMI ≥35 kg/m² randomised to either aerobic exercise, aerobic-strength exercises or control conditions found a greater reduction in weight, per cent body fat and fat mass in the intervention groups when compared with the control, which was statistically significant. Reduction in fat free mass was significantly lower in the aerobic-strength group when compared with the others.^12^ However, not everyone who undergoes bariatric surgery becomes more physically active. Evidence from a systematic review and meta-analysis identified that although self-report and objective physical activity (PA) increased at 12 months post surgery, this manifested as an increase in lower intensity PA and a reduction in moderate-to-vigorous intensity PA (MVPA).^13^ A longitudinal study compared levels of PA before surgery and 6 months thereafter using self-report and objective measures (accelerometery). Prior to surgery 10% of participants met the PA guidelines for health of 150 min/week MVPA according to both outcome tools. Post surgery this increased to 55% according to self-report but was not supported by accelerometer data which showed that only 5% of participants achieved this.^14^ Thus, it is likely that in post-surgical care, patients will report higher than actual levels of PA. Another behaviour of interest in this study is sedentary behaviour (SB). A transient increase in SB is associated with significant reductions in insulin sensitivity, decreased lower limb lean muscle mass and increased body fat,^15^ which is particularly relevant to this patient group who are already at risk of metabolic disease.

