## Aim and objectives

The lack of evidence for interventions to increase PA and reduce SB means that it would be inappropriate to progress to a full-scale evaluation trial, and thus a feasibility study is warranted.

The aim of this study is to assess the feasibility of single arm, physiotherapist led, online group-based behaviour change intervention to increase PA and reduce SB following bariatric surgery. Once we have conducted this study we will be able to determine if the intervention could be evaluated in a future definitive study.

The objectives relate to uncertainties and are as follows:

To ascertain recruitment and retention to the intervention and study.To investigate fidelity of the intervention, participant engagement with and acceptability of the intervention.To test the feasibility of study outcome measures: questionnaires, accelerometery and dual energy X-ray absorptiometry (DEXA) scan.To estimate the necessary sample size for a future evaluation study based on the chosen outcome measures.

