## Methods: participants, interventions and outcomes

### Patient and public involvement

A patient and public involvement (PPI) group, comprising three members who have previously undergone bariatric surgery, was recruited via Obesity UK at the start of development work and they have inputted into both the intervention and study design of this and previous studies, over approximately a 3-year period. They have helped to develop the research question, inputted into development work, helped to refine intervention objectives and have influenced study design. An example of this is their absolute rejection of the initial proposal to include randomisation to either the intervention or standard care group as they felt support to increase PA and reduce SB would be beneficial for anyone who had undergone bariatric surgery, thus randomisation was unacceptable.

In view of the strength of feeling from the PPI group, the current COVID-19 pandemic and the aims of this feasibility study, the team agreed with the PPI group not use a randomised design in this instance and to proceed with a single arm feasibility study. However, once we have the results of this study we will meet with the PPI group, explain the principle of equipoise and work with them on study design which will include determining an appropriate control condition. The contribution of the PPI group to this study has been invaluable, and they will continue to contribute through the trial management group (TMG) and in dissemination once the study is complete.

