### Sample size

This is a feasibility study and thus there is no formal sample size which has been calculated against a primary outcome measure. In future studies this is likely to be objectively measured PA or SB. A pragmatic sample size range has been set for 12–24 participants. Twelve is the minimum recommended sample size for a feasibility study^23^; successfully recruiting up to 24 participants would allow a more precise sample size calculation for a future trial.

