### Statistical methods

Quantitative data will be analysed descriptively and this will be used to calculate the sample size that would be required for a fully powered trial. Analysis will occur after the study is complete, thus there will be no interim analysis of data. As this is a feasibility study, the rate of missing data itself will be an outcome. Due to the size of the study, there is limited capacity to assess patterns of missingness across treatment groups or known prognostic factors.

Qualitative data will be collected and analysed concurrently. Descriptive analysis will be used to identify codes and overarching categories that they construct. Interpretive analysis will then be used to identify subthemes and themes to which they belong allowing a greater understanding of the participants’ experience of the intervention and the acceptability of this. This process will be iterative informed by the constant comparative approach of grounded theory,^26^ with the aim of generating greater understanding of participants’ experiences of the intervention.

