## Study status

Recruitment began in March 2021 and the study is ongoing. It is realistic to suggest that the study might still be impacted by COVID-19, which may result in it being deemed inappropriate for participants to access the research site. However, PARIS has been developed in such a way that it minimises the potential impact from COVID-19. Site visits have been reduced, and the intervention has been designed to be delivered online. If there are further COVID-19 disruptions, it might be possible for the study design to adapt to reduce site visit frequency or duration further, for example, sending out questionnaires and accelerometer via recorded delivery to avoid participants coming to the study site. This would be discussed, as appropriate with the PPI group, trial management group, study sponsor and the REC.

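### The future controlled trial is to be sized from the uncontrolled change seen in 12–24 people, which neither isolates the between-arm difference nor estimates it with useful precision

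*Protocol article*

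**What the plan says.** The abstract (Methods and analysis) lists physical activity (PA), sedentary behaviour (SB), body composition and self-reported health as secondary outcomes, to be described, and then states: "Change in these outcomes will be used to calculate the sample size for a future evaluation study". The fourth objective under Aim and objectives is "To estimate the necessary sample size for a future evaluation study based on the chosen outcome measures". Statistical methods says of the descriptive analysis that "this will be used to calculate the sample size that would be required for a fully powered trial".

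The Sample size section sets a pragmatic range of 12–24, says the future primary outcome is likely to be objectively measured PA or SB, and adds that "successfully recruiting up to 24 participants would allow a more precise sample size calculation for a future trial". It attaches no precision figure to that claim.

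The Patient and public involvement section records the decision "not use a randomised design in this instance and to proceed with a single arm feasibility study". It says that after this study the team will return to the patient group and "work with them on study design which will include determining an appropriate control condition".

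Nowhere does the article name a target or minimum important difference, or limit the use of the data to their variability.

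**The concern.** A controlled trial is sized on the difference between arms. A single-arm change contains that difference plus whatever would have happened anyway, and nothing in this design separates the two.

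The article itself gives reasons to expect background change. Eligibility runs from 8 weeks to 5 years after surgery. Background and rationale reports from a meta-analysis that "although self-report and objective physical activity (PA) increased at 12 months post surgery", and the same sentence adds that the rise was in lower-intensity activity while moderate-to-vigorous activity (MVPA) fell. Study status says "Recruitment began in March 2021 and the study is ongoing" and accepts that COVID-19 may still affect the study. The bias therefore has no known sign. For overall PA the observed change could overstate the effect of the intervention; for MVPA it could understate it.

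Separately, a mean from 12–24 people is a noisy target difference even without bias. The required sample size varies with the inverse square of that target, so the noise is magnified.

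What is at stake is the size of the next trial. The Introduction says that, to the authors' knowledge, no study in this field has been adequately powered for PA or SB.

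**Working it through.** **Plan's own figure.** There is none to reproduce. The range 12–24 is declared pragmatic, and no alpha, power, SD, effect size or future sample size is given.

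**Inputs.** From the article: n = 12 and n = 24; single arm; a future control condition. Assumed, because the article is silent: two-sided alpha 0.05, 80% power, 1:1 allocation, a two-sample t-test on change, equal SD in both arms, no dropout and no clustering. Effects are in units of the SD of change.

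**1. Precision of the mean change.** The 95% half-width is t(0.975, n−1)/√n.
- n=12: 2.201/√12 = 0.64 SD
- n=24: 2.069/√24 = 0.42 SD

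At n=12 an observed change of 0.5 SD has an interval that includes zero.

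**2. Bias alone (assumed values).** Suppose the observed change is 0.5 SD, of which 0.2 SD would also have occurred in controls, so the true difference is 0.3 SD. The number per arm is roughly 2(1.960+0.842)²/d² = 15.7/d², before the small t-test correction.
- Planned on 0.5: 15.7/0.25 = 63, or 64 with the correction
- Needed for 0.3: 15.7/0.09 = 174, or 176 with the correction
- Power at 64 per arm with d = 0.3: the non-centrality is 0.3 × √(64/2) = 1.70, which gives 39%

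The loss depends on the share of the change that also occurs in controls. From nominal 80%, power is about 56% at a 25% share, 39% at 40% (the example above) and 29% at 50%.

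**3. Sampling error alone.** The true difference is 0.4 SD with no bias (correct size about 100 per arm). Pilots were simulated and the trial sized for 80% power on each pilot's observed d. Pilots with d of 0.1 or less were set aside, because they would imply more than 15.7/0.01 = 1,570 per arm or no trial at all.

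| | n=12 | n=24 |
|---|---|---|
| Pilots set aside | 15% | 7% |
| Planned per arm, 10th–90th percentile | – | about 33–390 |
| Actual power below 50%, among retained pilots | about 35% | about 24% |
| Same, as a share of all pilots | 0.35 × 0.85 = 30% | 0.24 × 0.93 = 22% |

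**4. Fixed target, SD only from the pilot.** With a true difference of 0.5 SD and no bias, the chance that actual power falls below 40% is 19% (n=12) or 9% (n=24) when the observed change is the target. With the target fixed in advance it is about 3% or 0.2%.

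**5. Allowance for an uncertain SD.** The upper one-sided 80% limit multiplies the SD by √[(n−1)/χ²(0.20, n−1)].
- n=12: √(11/6.989) = 1.25, which multiplies the sample size by 11/6.989 = 1.57
- n=24: √(23/17.187) = 1.16, which multiplies the sample size by 23/17.187 = 1.34

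**The case against.** The strongest reply is that only the abstract speaks of change. The objective, the Sample size section and Statistical methods are all compatible with using the SD of change alone, and step 4 shows that the loss would then be small. This stands as a possible reading, but nothing in the article adopts it, and the one sentence that names the input names the change.

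A second reply is that every effect, and every share of background change, in the working is assumed. That is true, so the figures show what can happen and do not forecast it. If a quarter or less of the change is shared with controls, power stays at 56% or more before sampling error. The quoted meta-analysis also concerns 12 months after surgery, whereas here the sessions run over 6–8 weeks with follow-up about 6 weeks later, so background drift could be modest.

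A reader might infer more than the article supports:
- *That the trial will end at well under half its nominal power.* The 39% example is 0.49 of 80%. A figure of 29% requires half the change to be shared with controls, which nothing in the article establishes.
- *That the bias inflates the effect.* The fall in MVPA points the other way.
- *That regression to the mean is built in.* The eligibility criteria contain no activity threshold.
- *That the plan wrongly ignores group clustering or takes the SD at face value.* The article makes neither choice. Such detail can sit in a fuller document, and the future design is still open.

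Finally, the later trial will have its own protocol, and nothing about feasibility in the present study depends on this calculation. That bears on severity and does not remove the point.

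**Conclusion.** The concern holds as a stated but unsuitable use of the data. An uncontrolled change in 12–24 people does not estimate the between-arm difference of a controlled trial, its bias has no known direction, and its 95% interval is about ±0.42 to ±0.64 SD. On the assumptions above, it could lead to 64 per arm where 176 are needed (39% power). Even with no bias at n=24, it could give anything from about 33 to 390 per arm where about 100 is right.

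The imprecision follows from n alone. The power figures depend on the assumed effects and shares. If only the SD of change was intended, most of the problem disappears and what remains is a wording correction. Recruitment, retention, fidelity, engagement and acceptability are unaffected, so this should be fixed but does not undermine the present study.

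**What to change.** In the full protocol or analysis plan, and in any restatement of the abstract and Statistical methods sentences, replace the statement on sample size with wording such as:

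> The target difference for the future trial will be a minimum important difference in the chosen objective PA or SB outcome, set in advance and not taken from the change observed in this study. This study will supply the SD, entered at its upper one-sided 80% confidence limit (about 1.25 times the estimate at n=12 and 1.16 times at n=24), the baseline–follow-up correlation, and retention and missing-data rates. Observed change will be reported with its 95% confidence interval as description only.

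The article gives no minimum important difference, so the team must choose and justify one once it has settled on PA or SB. Analysis takes place only after the study is complete, so this can be settled before results are seen.

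The cost is a couple of sentences, with no new data, visits or participants. The downside is that the future sample size is likely to be larger, by about 1.34 times (n=24) to 1.57 times (n=12) from the SD limit alone.

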**Ethics and dissemination:**

This study has National Health Service Research Ethics Committee approval; Haydock 20/NW/0472. All participants will provide informed consent and can withdraw at any point. Findings will be disseminated through peer-reviewed journals, conference and clinical service presentations.

**Trial registration number:**

ISRCTN31524689.

Strengths and limitations of this studyThis is a pragmatic single arm study evaluating a theory and evidence-based group intervention, which was developed through evidence synthesis, review of relevant theory and qualitative research with the patient population, clinicians and commissioners.We have identified that it would be inappropriate to immediately progress to a full trial, and thus designed a single site feasibility study with our patient and public involvement group, that can answer study and intervention uncertainties.We have outlined our protocol for a group behaviour change intervention, delivered online to a clinically vulnerable patient group during a worldwide pandemic.

## Introduction

### Background and rationale

Obesity is defined as an excessive accumulation of adiposity that presents a risk to health, this is often indicated by a body mass index (BMI) greater than 30 kg/m².^1^ It is a non-communicable disease, and is associated with serious conditions including type 2 diabetes, cardiovascular disease, obstructive sleep apnoea and some cancers.^2^ Most recently the seriousness of obesity has been highlighted with data showing that people with obesity have an increased susceptibility to serious disease and mortality from COVID-19 when compared with the general population.^3 4^

The most effective treatment for severe obesity (BMI ≥35 with obesity-related complications or ≥40 without) is bariatric surgery. It rapidly induces significant weight loss and can improve complications of obesity such as type 2 diabetes.^5^ Surgery however is not a cure; weight can be regained so associated conditions can return,^6–8^ as a result there is increasing attention to long-term outcomes and how patients might be supported to optimise weight maintenance, physical function and to reduce complications of obesity in the longer term.^9^

Evidence from systematic reviews and meta-analyses shows that patients who are more physically active after bariatric surgery optimise their weight and fat mass loss and improved their fitness compared with those who do not.^10 11^ Evidence from a randomised control trial of 60 patients with a BMI ≥35 kg/m² randomised to either aerobic exercise, aerobic-strength exercises or control conditions found a greater reduction in weight, per cent body fat and fat mass in the intervention groups when compared with the control, which was statistically significant. Reduction in fat free mass was significantly lower in the aerobic-strength group when compared with the others.^12^ However, not everyone who undergoes bariatric surgery becomes more physically active. Evidence from a systematic review and meta-analysis identified that although self-report and objective physical activity (PA) increased at 12 months post surgery, this manifested as an increase in lower intensity PA and a reduction in moderate-to-vigorous intensity PA (MVPA).^13^ A longitudinal study compared levels of PA before surgery and 6 months thereafter using self-report and objective measures (accelerometery). Prior to surgery 10% of participants met the PA guidelines for health of 150 min/week MVPA according to both outcome tools. Post surgery this increased to 55% according to self-report but was not supported by accelerometer data which showed that only 5% of participants achieved this.^14^ Thus, it is likely that in post-surgical care, patients will report higher than actual levels of PA. Another behaviour of interest in this study is sedentary behaviour (SB). A transient increase in SB is associated with significant reductions in insulin sensitivity, decreased lower limb lean muscle mass and increased body fat,^15^ which is particularly relevant to this patient group who are already at risk of metabolic disease.

We have conducted a systematic review that has identified that to our knowledge, there have not been any studies that have been appropriately powered to detect a change in PA or SB in people who have undergone bariatric surgery. Our review included studies where an intervention was delivered either pre-bariatric or post-bariatric surgery as long as there were post-surgical measures of PA, SB or both.^16^ Much of the focus in the literature, is on the physiological effects of changing these target behaviours as opposed to how to facilitate changes. Where the effect of an intervention on these behaviours is considered it tends to be because they are part of a battery of outcome measures rather than being the primary outcome or behaviour of interest. Many interventions are poorly described in terms of the theory-base; behaviour change techniques are not always described according to the taxonomy and the rationale for their use is not clearly explained.^16^ This lack of detail makes replication of intervention conditions challenging. Furthermore, assessment of fidelity and review of engagement beyond recording the number of sessions attended makes it difficult to ascertain if the interventions have been delivered and received as intended.^17–19^ Thus, there is an evidence gap for interventions that aim to increase PA and reduce SB in patients who have undergone bariatric surgery that this study seeks to address.

To summarise, there is a need for high quality studies, based on theory and evidence that target PA and SB, must be accurately described, clearly communicated and transparently evaluated.

The proposed study is a feasibility study of a group, theory-based intervention delivered online using a widely available platform (Zoom) which will be supported by an intervention handbook.

The intervention development is robust; it is the result of evidence synthesis, review of relevant theory and qualitative research with the patient population, clinicians and commissioners. Evidence has been mapped against the Behaviour Change Wheel, which includes the COM-B model and the Theoretical Domains Framework.^20 21^ The intervention has eight objectives which will be met over the course of six intervention session, each of which will be 1–1½ hours in duration.

